# Local versus distal acupoint low-level light therapy for pain relief in primary dysmenorrhea: protocol for a randomized, assessor- and statistician-blinded, pilot study

**DOI:** 10.3389/fmed.2026.1793534

**Published:** 2026-05-19

**Keywords:** acupoint phototherapy, Korean medicine, low-level light therapy, multimodal biosignal, primary dysmenorrhea, randomized controlled trial

## Abstract

**Background:**

Primary dysmenorrhea (PD) is a common gynecological condition affecting a substantial proportion of women of reproductive age. Non-steroidal anti-inflammatory drugs often provide incomplete pain relief and may be associated with adverse effects (AEs), highlighting the need for low-risk, non-pharmacological alternatives. Low-level light therapy (LLLT) has emerged as a promising non-invasive modality for pain management; however, the comparative effects of LLLT applied to local versus distal acupoints remain unclear.

**Method:**

This is a single-center, prospective, randomized, assessor- and statistician-blinded, parallel-group pilot study. A total of 60 women with moderate-to-severe PD will be randomized to receive LLLT at either local or distal acupoints. Interventions will be administered once daily for 7 consecutive days prior to menstruation across three menstrual cycles. Pain intensity will be assessed using the visual analog scale (VAS). Multimodal biosignals, such as electrocardiography, electromyography, electrodermal activity, photoplethysmography, respiration, and skin temperature, will be recorded to explore physiological responses to treatment. The primary outcome is the change from baseline in VAS measured at the scheduled post-menstrual visit occurring within 3 days after the onset of menstruation, assessed across three menstrual cycles. The secondary outcomes include biosignal changes, patient-reported outcomes, and the Patient Global Impression of Change.

**Conclusion:**

To the best of our knowledge, this will be one of the first randomized studies to directly compare LLLT applied to local and distal acupoints in patients with PD. As a comparative pilot study, it is not designed to establish definitive efficacy but to explore differences between stimulation strategies and to generate preliminary data for future confirmatory studies.

**Study protocol registration:**

https://cris.nih.go.kr/cris/search/detailSearch.do?seq=30497&sea. This study has been registered with the Clinical Research Information Service, identifier KCT0010827 (registration date: 29 July 2025).

## Introduction

1

Primary dysmenorrhea (PD) is among the most prevalent gynecological complaints, affecting approximately 45–95% of women of reproductive age worldwide (1, 2). It is characterized by recurrent spasmodic lower abdominal pain during menstruation in the absence of identifiable pelvic pathology (3). Given its high prevalence and recurrent nature, PD imposes a substantial public health burden, significantly affecting daily activities, academic or work performance, and quality of life. Up to one-third of affected individuals report absenteeism or severe functional limitations during menstruation (1, 4). Accordingly, PD is increasingly recognized as a chronic pain condition with meaningful psychosocial and economic implications.

Current first-line treatments primarily include non-steroidal anti-inflammatory drugs (NSAIDs), which target prostaglandin-mediated uterine hypercontractility and ischemia (3, 5). However, approximately 20–25% of patients experience inadequate pain relief, and long-term use may be limited by gastrointestinal, renal, and cardiovascular adverse effects. Hormonal contraceptives represent an alternative option but may not be acceptable for individuals seeking fertility preservation or preferring non-hormonal approaches (6). These limitations have led to growing interest in safe, non-pharmacological interventions with improved tolerability and patient acceptability.

Low-level light therapy (LLLT), also referred to as photobiomodulation, has emerged as a promising non-invasive modality for pain management (7). Experimental and clinical studies have suggested that LLLT modulates cellular activity, improves microcirculation, and exerts anti-inflammatory and analgesic effects (7, 8). In PD, these mechanisms may help alleviate uterine ischemia and reduce smooth muscle hypercontractility. Preliminary clinical studies have reported reductions in menstrual pain following light therapy applied to the abdominal region, supporting its potential therapeutic role (9).

In traditional Korean medicine (TKM), acupoint-based interventions have long been used to regulate gynecological function and relieve menstrual pain. Local acupoints, such as CV4 (Guanyuan) and CV6 (Qihai), are traditionally associated with uterine regulation, whereas distal acupoints, including SP6 (Sanyinjiao), ST36 (Zusanli), and LI4 (Hegu), are believed to exert systemic regulatory effects (10, 11). With advances in medical technology, light-based stimulations have been increasingly applied to acupoints, integrating traditional meridian theory with modern photobiomodulation approaches. Compared with needle acupuncture, acupoint-based light therapy offers advantages such as non-invasiveness, standardization, and improved patient acceptability, supporting its potential as an electroceutical intervention in integrative gynecology (12).

Despite growing clinical interest, previous randomized controlled trials (RCTs) have primarily evaluated LLLT in comparison with sham or standard care, focusing on efficacy outcomes (13–15). However, key treatment parameters, particularly the optimal selection of stimulation sites, remain insufficiently understood. It remains unclear whether targeting local uterine-associated acupoints or distal systemic acupoints results in differential therapeutic outcomes in PD. This gap is clinically relevant, as both approaches are commonly used in practice but may involve distinct mechanisms, including local physiological modulation and systemic or central pain regulation.

Therefore, this study was designed as a comparative pilot randomized trial to explore potential differences between local and distal acupoint stimulation, rather than to establish efficacy. The primary objective is to generate preliminary data to inform treatment optimization and the design of future confirmatory studies. Multidimensional outcomes, including psychosocial and quality-of-life measures, will also be assessed to better capture the broader impact of PD.

## Methods and analysis

2

### Aim

2.1

This study aimed to compare the effects of LLLT applied to local versus distal acupoints on menstrual pain in women with PD.

### Study design

2.2

This study is a randomized, assessor- and statistician-blinded, two-arm, parallel-group pilot study designed in accordance with the Standard Protocol Items: Recommendations for Interventional Trials (SPIRIT) 2025 statement (16). The results of the study will be reported in accordance with the Consolidated Standards of Reporting Trials (CONSORT) 2010 guidelines (17).

Participants who provide written informed consent will undergo eligibility screening, and a total of 60 participants will be enrolled for a 12-week study period (Figure 1).

**Figure 1 fig1:**
[figure not shown]
Study design flowchart. Flow diagram of the RCT comparing the local acupoint group and the distal acupoint group in 60 patients with PD. Participants were randomly assigned to receive low-level light therapy at either local or distal acupoints.

This study adopts a comparative design without a sham or usual-care control group, as its primary objective is to explore differences between intervention strategies rather than to evaluate absolute efficacy.

The study protocol will adhere to the Declaration of Helsinki and Good Clinical Practice guidelines and has been approved by the Institutional Review Board of Woosuk University Jeonju Korean Medicine Hospital [Version 1.0, Reference Number: Institutional Review Board of Woosuk University Jeonju Korean Medicine Hospital (WSOH IRB) M2507-01]. All study procedures will be conducted at the Woosuk University Jeonju Korean Medicine Hospital in South Korea.

Any important modifications to the study protocol will be submitted to the IRB for approval prior to implementation and will be communicated to relevant parties, including investigators and trial registries, as required.

Written informed consent will be obtained from all participants by trained research personnel prior to enrollment. Participants will be provided with detailed information about the study procedures, potential risks, and benefits.

Recruitment is scheduled to begin in October 2025 and is expected to be completed by October 2026. Data collection and analysis are anticipated to be completed in the first half of 2027. Participants will be allocated in a 1:1 ratio to either the local or distal acupoint group. To assess effectiveness and safety, participants will attend visits at the onset of menstruation across three menstrual cycles. Detailed study procedures are presented in Table 1.

**Table 1 tab1:** Schedule of enrollment, interventions, and assessments in accordance with the SPIRIT statement.

Timepoint	Enrollment	Allocation	Post-allocation					Close-out
	Screening	Run-in period	Cycle 1 (4 weeks)		Cycle 2 (8 weeks)		Cycle 3 (12 weeks)	
Visit (Visit window)	Visit 0 (−2 weeks ± 2 days)	Visit 1 (−1 week ± 2 days)	1st self-treatment (7 days)	Visit 2 (menses + 3 days)	2nd self-treatment (7 days)	Visit 3 (menses + 3 days)	3rd self-treatment (7 days)	Visit 4 (menses + 3 days)
Enrollment								
Informed consent	●							
Demographics	●							
Menstrual history	●							
Medical and treatment history (including medication use)	●							
Physical examination	●							
Vital signs	●	●		●		●		●
Anthropometrics	●							
Laboratory tests (blood)^a^	●							
Pregnancy test	●							
Visual analog scale (VAS) for pain	●	●		●		●		●
Beck Depression Inventory-II (K-BDI-II)	●	●		●		●		●
Inclusion/exclusion criteria	●							
Allocation								
Randomization		●						
Intervention^b^								
Home-based LLLT at local acupoint (self-administration, daily for 7 days premenstrual)			●		●		●	
On-site LLLT at local acupoint				●		●		●
Home-based LLLT at distal acupoint (self-administration, daily for 7 days premenstrual)			●		●		●	
On-site LLLT at distal acupoint				●		●		●
Assessment								
Quality of life (EQ-5D-5L)		●		●		●		●
Stress response inventory-short form (SRI-SF)		●		●		●		●
State–trait anxiety inventory (STAI)		●		●		●		●
Device dispensing and training for home-based self-administration		●						
Clinical device return								●
Analgesic use check (type and dose)		●		●		●		●
Menstrual diary (distribution/collection)		●		●		●		●
Multimodal biosignal measurements^c^				●		●		●
Compliance with home-based LLLT				●		●		●
Patient Global Impression of Change (PGIC)								●
Changes in medical/treatment history		●		●		●		●
Adverse events				●		●		●
End of study/case closure								●

^a^If laboratory test results within 2 weeks prior to screening are available, they may be used in place of repeat testing at screening. Tests include complete blood count (CBC), liver function tests [such as total bilirubin, total protein, albumin, aspartate transaminase (AST), alanine transaminase (ALT), alkaline phosphatase (ALP), and gamma-glutamyl transferase (GGT)], renal function (such as BUN and creatinine), thyroid function (TSH), and HbA1c. ^b^Low-level light therapy will be performed as home-based self-administration once daily for 20 min during the 7 days prior to menstruation, followed by a single on-site supervised session at each cycle visit. Participants will record light therapy adherence and pain levels in the provided diary. ^c^Multimodal biosignal measurements (on-site only: pre−/during/post-stimulation). Biosignal monitoring will include six parameters: respiration (RSP), electrocardiogram (ECG), photoplethysmography (PPG), electrodermal activity (EDA), skin temperature (SKT), and electromyography (EMG). SPIRIT, Standard Protocol Items: Recommendations for Interventional Trials.

### Participants

2.3

#### Target disease

2.3.1

PD (ICD-10 N94.4) will be diagnosed based on clinical assessment, defined as recurrent menstrual pain in the absence of known pelvic pathology. Eligible participants must report a consistent history of dysmenorrhea over the previous 3 months and have a regular menstrual cycle. Routine imaging studies, such as ultrasound, will not be performed unless clinically indicated to exclude secondary causes.

To reduce clinical and physiological heterogeneity, relatively restrictive eligibility criteria were applied. Given the exploratory nature and small sample size of this pilot study, minimizing variability was considered important to improve the interpretability of between-group comparisons. While this approach may limit generalizability, it was deemed appropriate to enhance internal validity and is consistent with methodological recommendations for pilot studies emphasizing feasibility and preliminary effect estimation rather than definitive hypothesis testing (18).

Furthermore, participants will be clinically screened by investigators to exclude features suggestive of secondary dysmenorrhea, and individuals with suspected underlying pelvic pathology will not be enrolled.

The detailed inclusion and exclusion criteria are as follows:

#### Inclusion criteria

2.3.2

Women aged 19–45 years with regular menstrual cycles and diagnosed with moderate-to-severe PD [visual analog scale (VAS) ≥ 40 mm for at least 3 cycles] will be included (19, 20). The exclusion criteria are secondary dysmenorrhea, chronic pelvic pain, use of hormonal contraceptives, or ongoing light-based therapy.

The inclusion criteria are as follows: (1) women aged 19–45 years; (2) individuals who have consistently experienced PD (menstrual pain) over the past 3 months, with a menstrual pain VAS score of 40 mm or higher; (3) individuals with a regular menstrual cycle ranging from 21 to 35 days (28 ± 7 days) over the past 3 months; and (4) individuals who have voluntarily provided written informed consent to participate in the clinical study.

#### Exclusion criteria

2.3.3

The exclusion criteria were grouped into the following categories:

Psychiatric conditions or related medication use: participants were excluded if they had a history of major psychiatric disorders within the past 2 years, were currently using psychotropic medications including antidepressants, or were suspected of having moderate-to-severe depression based on the Korean version of the Beck Depression Inventory-II score of ≥23.

Gynecologic, reproductive, or hormone-related factors: participants were excluded for use of oral contraceptives or other hormone therapy within 3 months before screening; structural abnormalities that may cause dysmenorrhea, including uterine fibroids, ovarian cysts, endometriosis, or cervical stenosis; treatment for uterine inflammatory conditions, including endometritis or cervicitis, within 2 months before screening; use of an intrauterine contraceptive device; or pregnancy, breastfeeding, planned pregnancy, or potential pregnancy without medically acceptable contraception during the study period.

Clinically significant medical conditions or abnormal screening results: participants were excluded for thyroid disease or abnormal thyroid function, defined as thyroid-stimulating hormone level of ≤0.26 or ≥4.3 μIU/mL; severe hepatic or renal impairment or abnormal laboratory findings, including aspartate aminotransferase or alanine aminotransferase of ≥2 × the upper limit of normal [ULN], blood urea nitrogen of ≥2 × ULN, or creatinine of ≥2.0 mg/dL; malignancy within the past 5 years; hemoglobin of <11 g/dL or current treatment for anemia; uncontrolled hypertension, defined as systolic blood pressure of ≥180 mmHg or diastolic blood pressure of ≥110 mmHg; uncontrolled diabetes mellitus, defined as hemoglobin A1c of ≥9%; or any uncontrolled serious systemic disorder or infectious disease, including cardiovascular, respiratory, gastrointestinal, genitourinary, neurological/psychiatric, hematological, endocrine, or autoimmune diseases.

Device-related or procedural limitations: participants were excluded if they had known hypersensitivity or allergic reaction to the investigational medical device or if they were unable to self-administer the device as required because of compliance issues or other limitations.

Other reasons: participants were excluded if they had participated in another clinical study involving investigational medical devices or drugs for pain relief within 3 months before screening or if they were deemed unsuitable for the study by the investigator for any other reason.

#### Analgesic handling

2.3.4

The use of rescue analgesics (such as NSAIDs) will be permitted as needed and will be systematically recorded, including timing, frequency, and dosage. Analgesic use within a predefined time window prior to VAS assessment will be included as a covariate in the primary analysis to account for its potential immediate effect on pain reporting.

All medication use will be recorded throughout the study period. In addition, cumulative analgesic use during the assessment period will be considered in sensitivity analyses.

Participants will be instructed to refrain from receiving other treatments for dysmenorrhea, including additional light therapy, transcutaneous electrical nerve stimulation, acupuncture, or other physical or complementary therapies, during the trial period.

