### Sample size

2.7

As this study is an exploratory pilot trial, the sample size was determined primarily based on feasibility considerations and the need to obtain preliminary estimates for a future confirmatory randomized controlled trial, rather than to test a definitive efficacy hypothesis. We therefore did not base the sample size on a formal power calculation. A total of 60 participants, with 30 participants per group, was considered appropriate for evaluating key feasibility parameters, including recruitment, adherence, retention, safety, and completion of outcome assessments. This sample size was also expected to provide preliminary estimates of treatment effect and variability, which will be used to inform the design and sample size calculation of a future adequately powered confirmatory trial. Allowing for an anticipated dropout rate of approximately 20%, the target enrollment was set at 60 participants in total.

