#### Primary outcome

2.8.1

The primary outcome is the change from baseline in menstrual pain intensity measured using a 0–100-mm VAS (26). The primary endpoint is defined as the change from baseline in VAS measured at the scheduled post-menstrual visit occurring within 3 days after the onset of menstruation, assessed across three menstrual cycles.

A visit window of up to 3 days after menstruation onset is allowed to accommodate inter-individual variability in the timing of peak pain and to ensure feasibility while minimizing protocol deviations. Assessments will be conducted at baseline and at each post-menstrual visit (visit window: day 1 + 3 days) over three menstrual cycles.

To further characterize individual pain patterns, VAS scores will be recorded daily from 7 days prior to menstruation through the first 3 days of menstruation. Sensitivity analyses will be conducted using alternative outcome definitions, including the maximum VAS during menstrual days 1–3.

To evaluate treatment effects, a linear mixed-effects model (LMM) will be used, with treatment group, visit (time point), and group-by-visit interaction specified as fixed effects, and participant-level variability included as a random effect. Baseline VAS will be included as a covariate (27).

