#### Secondary outcomes

2.8.2

The secondary outcomes include changes in biosignals and patient-reported outcomes, such as the Korean version of the Beck Depression Inventory-II (K-BDI-II) (28), the EuroQol 5-Dimension 5-Level (EQ-5D-5L) (29), the Stress Response Inventory-Short Form (SRI-SF) (30, 31), and the State–Trait Anxiety Inventory (STAI) (32) assessed at baseline and at each post-menstrual visit (visit window: day 1 + 3 days) over three cycles. PGIC will be assessed once at the final visit (33).

Multimodal biosignals: Multimodal biosignals will be acquired at baseline and at each post-menstrual visit over three menstrual cycles, including RSP, ECG, PPG, EDA, SKT, and EMG. Biosignal measurements will be analyzed as exploratory outcomes. The underlying hypothesis is that stimulation at different acupoint locations may induce differential modulation of physiological responses. Given the exploratory nature of these analyses, no formal adjustment for multiple comparisons will be applied, and the findings will be interpreted as hypothesis-generating.

K-BDI-II: The K-BDI-II is the validated Korean translation of the Beck Depression Inventory-II, a widely used self-reported measure of depressive symptoms. It consists of 21 items, each scored on a 4-point Likert scale (0–3), reflecting symptom severity over the past 2 weeks. Total scores range from 0 to 63, with higher scores indicating more severe depressive symptoms. Standard cutoff scores are defined as minimal (0–13), mild (14–19), moderate (20–28), and severe (29–63).

EQ-5D-5L: The EQ-5D-5L is a standardized instrument for assessing health-related quality of life. It comprises five dimensions: mobility, self-care, usual activities, pain/discomfort, and anxiety/depression. Each dimension is rated on five levels (from no problems to extreme problems). Responses are converted into a single index score using country-specific value sets, with higher scores indicating better health status. In addition, the EQ-5D-5L includes a visual analog scale (VAS; 0–100) for self-rated overall health.

SRI-SF: The SRI-SF is a validated short-form instrument used to assess multidimensional stress responses. It consists of 22 items scored on a 5-point Likert scale (0–4), covering emotional, somatic, cognitive, and behavioral domains. Total scores range from 0 to 88, with higher scores indicating greater stress response levels.

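### Rescue analgesic use, which the allocated site may affect, enters the plan only as a covariate and in a sensitivity analysis; no between-arm estimate of it is stated.

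*Protocol article*

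**What the plan says.** Section 2.3.4 permits rescue analgesics such as NSAIDs when needed and says their use "will be systematically recorded, including timing, frequency, and dosage". Table 1 schedules an "Analgesic use check (type and dose") at Visits 1 to 4.

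Sections 2.3.4 and 2.9.3 give these data the same two roles:

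- Use within a window before the VAS, to be fixed in advance, is a covariate in the primary mixed model. Section 2.9.3 gives the reason as adjustment for confounding.
- For the other role, section 2.3.4 says that "cumulative analgesic use during the assessment period will be considered in sensitivity analyses". The exposure is named. The model and the way it enters are not.

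Analgesic use is not the primary outcome (2.8.1). Section 2.8.2 opens with "The secondary outcomes include changes in biosignals and patient-reported outcomes" and goes on to name four questionnaires, the PGIC and six biosignals, but not analgesic use. Section 2.9.3 gives models for the primary and secondary outcomes and states no comparison of analgesic use by arm.

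Section 2.7 says the trial should give "preliminary estimates of treatment effect and variability, which will be used to inform the design and sample size calculation" of a later confirmatory trial.

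**The concern.** A confounder is a common cause of exposure and outcome. Randomised allocation has no such cause among events that follow it. A woman takes a rescue dose after randomisation because she is in pain, and that pain may depend on the site treated. Rescue use is then partly a consequence of the allocation.

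Two things follow. The group coefficient in the primary model compares arms at equal recent analgesic use, which is not the overall effect of assigning one site or the other. And if women at one site reach a similar VAS with fewer tablets, that benefit lies in the analgesic data, where no stated analysis looks for it.

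The introduction and rationale justify the trial by the limits of NSAIDs, so needing fewer of them is a result its readers would want. The estimates are also meant to plan the next trial. A small VAS difference could be read as little difference between sites while a difference in rescue use goes unreported.

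**Working it through.** The plan states no figure on this point, so there is none to reproduce. The text check is the side-by-side reading above: two roles for analgesic use, no outcome status and no by-arm comparison. The numbers below are illustrations. The article gives only 30 women per arm, about 20% dropout (30 × 0.8 = 24 per arm) and three cycles; everything else is assumed.

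**1. Why the covariate does not settle the matter.** Suppose the arms do not differ in pain without rescue, 30% use rescue in one arm and 60% in the other, and a dose lowers the VAS by 20 mm. The unadjusted VAS difference is 20 × (0.60 − 0.30) = 6.0 mm against the arm that used less (6.1 mm when simulated). Adjusted for use, it is 0.0 mm if use is unrelated to current pain, and 6.6 mm if use is driven by pain. Neither result displays the 30-point difference in use. With equal use in both arms, adjusted and unadjusted estimates agree.

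**2. What happens to a real difference.** Assume a true difference of 10 mm in pain without rescue, mean 55 mm, between- and within-woman SD 15 mm each, and three cycles. Change in VAS is modelled on group, visit and baseline with a random intercept. In a large simulated sample:

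- *Fixed analgesic effect of 15 to 35 mm, use more likely with more pain, 50 to 100% of users dosing in the window.* Window covariate: 5.1 to 9.3 mm. Any-use covariate: 4.9 to 8.0 mm. No covariate: 3.7 to 8.9 mm. Any use is 56 to 59% against 41 to 44%, a gap of 12 to 18 points.
- *Dosing down to a target level of 20 to 40 mm, window covariate.* If all women share one level and every dose falls in the window: 0.1 to 1.0 mm. With woman-specific levels (SD 10 to 20 mm): 0.6 to 2.6 mm. If only 50 to 75% of users dose in the window: 4.2 to 8.0 mm.

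The VAS contrast is attenuated with or without the covariate. Dropping the covariate would not recover the missing part; use itself has to be compared.

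**3. Precision of a by-arm comparison of any use.** Half-width = 1.96 × √[(p₁q₁ + p₂q₂)/m], where m = 3n/(1 + 2 × ICC). With ICC 0.5, m = 90/2 = 45 for n = 30, and 72/2 = 36 for n = 24. Worked case, 88% against 76%: √[(0.1056 + 0.1824)/45] = 0.080, and 1.96 × 0.080 = 15.7 points.

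| Assumed any use | Difference | Half-width, n = 30 | Half-width, n = 24 |
|---|---|---|---|
| 95% vs 88% | 7 | 11.4 | 12.8 |
| 88% vs 76% | 12 | 15.7 | 17.5 |
| 76% vs 59% | 17 | 19.0 | 21.3 |
| 50% vs 50% (widest) | 0 | 20.7 | 23.1 |

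In each of the first three rows the half-width exceeds the difference.

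**4. Precision for doses.** With 0.3 to 0.75 doses per day and woman-level log-SD 0.5 to 0.8, the 95% interval for the rate ratio is the estimate times or divided by 1.42 to 1.95. At a ratio of 0.75 the best case has an upper limit of 0.75 × 1.42 = 1.07.

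**5. Visit timing.** Visits 2 to 4 may fall from menstrual onset to 3 days later. In the same runs, any use up to the visit is 21 to 46% when it falls on day 1 and 53 to 87% on day 4. The number of observed days must therefore enter the model.

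**The case against.** The strongest reply is that this is an omission from a condensed article. A full version 1.0 protocol exists, an analysis plan may exist, and either could tabulate rescue use by arm. The secondary outcome list is also worded openly. This stands as a limit: a reader might infer that analgesic sparing will never be estimated, and the article cannot show that. What the article does show is a chosen role. It has a section on analgesics, names its outcomes, and calls a post-randomisation variable a confounder.

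A reader might also infer that the sensitivity analyses are wholly unspecified, or that the VAS contrast will nearly vanish. The first is wrong, because cumulative use is named as the exposure. The second needs every woman to dose to much the same level with every dose in the window, and the article says nothing about how women dose. In the fixed-effect illustration the planned covariate gives a somewhat higher range than no covariate (5.1 to 9.3 against 3.7 to 8.9 mm), so it may reduce the attenuation.

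The remaining objections limit the remedy without defeating it. The new estimate would be imprecise and partly driven by visit timing, and observed days are themselves measured after randomisation. Section 2.8.1 says "VAS scores will be recorded daily from 7 days prior to menstruation through the first 3 days of menstruation" and plans a sensitivity analysis on the maximum over menstrual days 1 to 3. That depends less on one possibly medicated visit, but it does not measure analgesic use. Finally, this is an exploratory pilot and the data are recorded, so the comparison could be made later; prespecifying it now is better than choosing it after seeing the VAS result.

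**Conclusion.** The point holds in a limited form. The plan as shown conditions its primary VAS contrast on a variable that treatment may affect, labels this confounder adjustment, and states no between-arm estimate of that variable. Any analgesic-sparing difference between sites is therefore not estimated in the text available.

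How much the VAS contrast is changed is unknown. The range of 5.1 to 9.3 mm for a true 10 mm rests on assumed pain levels, analgesic effects and dosing patterns, and other assumed patterns give less. The documents support neither the claim that the primary result is invalid nor the claim that the added outcome would detect a difference: under the assumptions used, its interval is likely to be wider than a plausible difference. The change is worth making because it is cheap and the estimates feed the next trial. It is not a fatal defect in an exploratory pilot.

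**What to change.** - **Section 2.8.2:** add analgesic use per cycle (any use; number of doses) as a secondary or exploratory outcome. Count it from menstrual onset to the VAS assessment at Visits 2, 3 and 4, using the recorded medication data. Table 1 describes the diary only as a record of adherence and pain, so it should not be assumed to hold doses. The window stops at the visit because Visit 4 closes the study.
- **Section 2.9.3, analgesic use:** estimate the between-arm difference with a GLMM containing group, visit, group-by-visit interaction and a random participant effect. Use a logistic model for any use with observed days as a covariate, and a count model for doses with log observed days as offset. Report it with a 95% confidence interval beside the VAS result, as descriptive and not powered. Do not use the Visit 1 check as a baseline: it falls in run-in and is not a comparable menstrual window.
- **Section 2.9.3, VAS:** report the model without the post-randomisation analgesic covariate as a sensitivity analysis, and stop describing the covariate as adjustment for confounding.

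The cost is some wording, one table and one more model run on data already recorded. The downside is one more imprecise outcome (half-width for any use roughly 11 to 23 points under the assumptions above), partly driven by visit timing and without a comparable pre-treatment baseline.
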